##### 2.4.1.1. Clinician-Administered PTSD Scale for DSM-5 (CAPS-5)

The Dutch version of the CAPS-5 (58, 59) is a clinician rated structured interview to assess PTSD diagnosis and symptom severity over the past month. The severity of each symptom is scored on a 0–4 scale. A sum score is computed and can range from 0 to 80. The CAPS-5 is considered to be the golden standard for assessing PTSD and shows high internal consistency and modest interrater reliability (60).

##### 2.4.1.2. PTSD Checklist for DSM-5 (PCL-5)

The Dutch version of the PCL-5 (61, 62) will be used to measure PTSD symptom severity over the past week. The PCL-5 is a 20-item self-report measure with total scores ranging from 0 to 80, and is widely used in scientific papers, which improves the comparability of the results. The monthly version of the PCL-5 has good internal consistency, test-retest reliability, and convergent and discriminant validity (63). The weekly version of the PCL-5 is currently still undergoing psychometric evaluation (64).

##### 2.4.1.3. International Trauma Questionnaire (ITQ)

To assess complex PTSD (CPTSD) symptoms and diagnosis, the Dutch version of the ITQ (65, 66) will be used. The ITQ is an 18-item self-report measure with total scores ranging from 0 to 72. The ITQ has demonstrated high internal consistency and has shown to measure reliable and clinically significant treatment-related change of ICD-11 CPTSD symptoms (67).

#### 2.4.2. Secondary outcome measures

Secondary study parameters are comorbid symptoms such as depression, experiential avoidance, treatment acceptability, and moderators of treatment effectiveness, which are measured with several self-report measures.

##### 2.4.2.1. Beck Depression Inventory-II (BDI-II)

The Dutch version of the BDI-II (68, 69) is a self-report measure that assesses symptoms of depression with 21 items. Total scores range from 0 to 63. This score can be used to assess the presence and severity of symptoms of depression. The BDI-II has been shown to have good psychometric properties (69).

##### 2.4.2.2. Dissociative Experiences Scale (DES)

The Dutch version of the DES (70, 71) will be used to measure several symptoms of dissociation. It is a 28-item self-report measure with an average total score ranging from 0 to 100. A higher score is interpreted as a higher level of dissociation and a cut-off score of 25 is indicative for the presence of a dissociative disorder (72). The Dutch DES has good internal consistency and good criterion validity (71).

##### 2.4.2.3. Brief Symptom Inventory (BSI)

The Dutch version of the BSI (73, 74) is a 53 item self-report measure that assesses general psychiatric symptoms. Total scores range from 0 to 212 and can be used to indicate the severity of psychopathology on several dimensions. The BSI has shown good reliability and validity (75).

##### 2.4.2.4. Acceptance and Action Questionnaire-II (AAQ-II)

The Dutch version of the AAQ-II (76, 77) is a 7-item self-report measure that assesses experiential avoidance. Total scores range from 7 to 49. The Dutch AAQ-II has been demonstrated to have adequate reliability and variability (77).

##### 2.4.2.5. Treatment acceptability

Treatment acceptability is assessed with four questions based on Tarrier et al. (78) and Devilly (79) which measure several facets which could be grouped under treatment acceptability. Three questions are: “How did you experience treatment?” The answer options range from 1 (very unpleasant) to 7 (very pleasant), from 1 (very intrusive) to 7 (not intrusive at all), and from 1 (very tiring) to 7 (not tiring at all). The fourth question is: “How likely is it that you would recommend the treatment to someone with the same symptoms?,” with answer options that range from 1 (very unlikely) to 7 (very likely). As the questions combined have not been validated as a questionnaire measuring the full concept of treatment acceptability, the items will be scored and interpreted separately instead of computing a total score.

##### 2.4.2.6. Moderators

Moderators of treatment effectiveness to be investigated are: symptoms of dissociation, experiential avoidance, the presence of a complex PTSD diagnosis, PTSD symptom severity, and symptoms of depression. All moderators are assessed at baseline using the DES, AAQ-II, ITQ, CAPS-5, and BDI-II, respectively.

#### 2.4.3. Other measures

##### 2.4.3.1. Life Events Checklist for the DSM-5 (LEC-5)

The Dutch version of the LEC-5 (80, 81) is a 17-item questionnaire which measures the exposure to 16 different A-criterion events which are known to potentially result in PTSD, with an additional option for another stressful event. Answer options include: “Happened to me,” “witnessed it,” “learned about it,” “part of my job,” “not sure,” and “doesn’t apply.” It is used to assess the type of traumatic events participants have experienced. The psychometric properties of the LEC-5 have not yet been investigated. However, the LEC-5 differs little from the LEC for DSM-IV, which has adequate psychometric properties (82).

### 2.5. Sample size

To perform a power analysis for a multilevel model, it is required to estimate parameters based on earlier research (83), which was not possible for the interventions investigated in the current study. Power analyses were performed in G*Power 3.1.9.2, based on three pairwise comparisons between the conditions (EMDR therapy vs. EMDR 2.0, EMDR therapy vs. Flash, EMDR 2.0 vs. Flash) on the post-treatment measurement occasion. The power analysis is based on a two-sided *t*-test, in which two independent means will be compared with a Bonferroni-corrected alpha for the three pairwise comparisons = 0.0167 (0.05/3), power = 0.80 and Allocation ratio = 1. We aim to be able to detect a clinical meaningful difference between the conditions, what comes down to a medium to large effect size *d* = 0.65. To increase the power, we will include the baseline CAPS-5 score as a covariate in the analyses (84). By doing so, we expect to explain approximately a quarter of the variance at the post-treatment measurement. The residual variance reduces and gives us a sample size of *n* = 39 per condition, or *N* = 117 in total. To account for an expected 10% dropout, we will recruit a total 130 participants.

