#### 2.6.1. Aim 1: Treatment effectiveness

##### 2.6.1.1. Outcome measures CAPS-5, ITQ, and DES

To investigate the effectiveness of the three treatment conditions, the average scores will be estimated for the outcome variables at each time point for the three conditions. The baseline values will be included as covariate in the model. This will result in 3 (Condition: EMDR, EMDR 2.0, and Flash) × 2 (Time: T8 and T12) average score estimates. To investigate the differential effectiveness in reducing PTSD, complex PTSD and symptoms of dissociation of the treatments, these average score estimates will be compared across the three conditions. To answer the research question if the treatment arms are effective in reducing PTSD, complex PTSD, and symptoms of dissociation over time, the average scores of measurement occasions T0 vs. T8 and T0 vs. T12 will be compared using *t*-tests.

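### Plain Bonferroni at 0.0167 is valid for the three pairwise comparisons but needlessly conservative with exactly three arms; a closed (Shaffer) test gains power at the same familywise error

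*Protocol article*

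**What the plan says.** Section 2.5 of the protocol article (Sample size) describes its power analyses as "based on three pairwise comparisons between the conditions", that is, all three pairs of arms at the post-treatment occasion, with a "Bonferroni-corrected alpha for the three pairwise comparisons = 0.0167 (0.05/3"). The other inputs are a two-sided t-test, "power = 0.80 and Allocation ratio = 1", an effect size of 0.65, and a baseline CAPS-5 covariate of which the authors write that "we expect to explain approximately a quarter of the variance at the post-treatment measurement". The result is 39 per condition and 117 in total, raised to 130 for dropout.

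Section 2.6.1.1 describes the between-arm analysis of CAPS-5, ITQ and DES. Estimates at T8 and T12 are adjusted for baseline, and "these average score estimates will be compared across the three conditions". It gives no testing procedure beyond that. The only multiplicity rule in the article is the Bonferroni level in section 2.5.

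**The concern.** Bonferroni treats the three pairwise hypotheses as if any combination of them could be true. In a three-arm trial that is not so. If EMDR equals EMDR 2.0 and EMDR equals Flash, then EMDR 2.0 equals Flash. The number of true null hypotheses can be three, one or none, but never two. Once one real difference has been established, at most one pairwise null can still be true, and holding the remaining comparisons to 0.0167 protects against nothing.

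At stake is power for the second and third comparisons. The trial is sized only for a medium-to-large difference, and the Discussion concedes that small differences will be missed. If the ranking of three treatments is the question, a procedure that recovers power without recruiting anyone and without raising the familywise error is worth having.

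**Working it through.** **Inputs, all from section 2.5.** Per-comparison level 0.05/3 = 0.0167, two-sided; power 0.80; d = 0.65; about 25% of variance explained by the baseline covariate; 10% dropout.

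**Reproducing the plan's figure.** The adjusted effect is 0.65/√(1 − 0.25) = 0.65/0.866 = 0.7506. For a two-sample t-test (noncentral t) at 0.05/3, power is 0.792 with 38 per arm and 0.804 with 39. So n = 39 per arm, 3 × 39 = 117, and 117/0.90 = 130. The plan's figures are right.

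**The closed test.** Call the pairwise nulls H12, H13 and H23. The intersection of any two is the global null H123. By the closure principle, a pair may be rejected at 5% familywise if its own p-value is at or below 0.05 and a valid 5% test of H123 also rejects. If H123 is tested by Bonferroni, it is rejected when the smallest p-value is at or below 0.05/3. This gives the Shaffer rule: smallest p at or below 0.0167, then the other two at 0.05.

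**Why it cannot lose to Bonferroni.** If Bonferroni rejects a pair, that pair's p-value is at or below 0.0167, so the gate is open and the pair also passes 0.05. If no p-value reaches 0.0167, both methods reject nothing. The two methods therefore make at least one rejection in exactly the same data sets, and they differ only in how many further pairs are declared.

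**Size of the gain.** Simulation used 500,000 trials per pattern, 39 per arm, adjusted d = 0.7506 and pooled residual variance with 3 × 39 − 4 = 113 df. Pooling over three arms is why Bonferroni shows 0.81 here rather than 0.804.

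| Pattern and quantity | Bonferroni | Shaffer | F-gated |
|---|---|---|---|
| One arm differs: power per true pair | 0.81 | 0.87 | 0.89 |
| One arm differs: both true differences found | 0.70 | 0.83 | 0.84 |
| One arm differs: at least one true difference found | 0.92 | 0.92 | 0.93 |
| Evenly spread: extreme pair | 0.81 | 0.82 | 0.84 |
| Evenly spread: each half-distance pair | 0.22 | 0.36 | 0.37 |
| Evenly spread: at least one difference found | 0.83 | 0.83 | 0.84 |
| Familywise error, all arms equal | 4.4% | 4.4% | 5.0% |
| Familywise error, one pair equal | 1.7% | 5.0% | 5.0% |

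The F-gated version tests the 2-df condition effect at 0.05 and then each pair at 0.05. It has slightly more power in both patterns but does not dominate Bonferroni case by case: in 0.1% to 0.4% of simulated trials it missed a pair that Bonferroni declared.

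**The same gain as sample size.** For 80% power on a pair that differs by the full d, Bonferroni needs 39 per arm. Shaffer needs 33 if one arm differs and 38 if the arms are evenly spread.

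**The case against.** The strongest reply is that nothing here is wrong. Bonferroni is valid and common, the sample size reproduces, and every full-size pair has its planned 80% power. That stands: this is a point of efficiency, not an error.

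The second reply is that the larger gains depend on a favourable pattern of means. That also stands. Section 1.4 declares no prior expectation about which treatment works better, so the document gives no support for one arm differing from two equal arms. With evenly spread arms the full-size pair gains about one percentage point. The half-distance pairs gain about 14, but they concern differences of 0.325, half of what the plan calls clinically meaningful, and remain poorly powered at 0.36. The chance of finding at least one difference does not move.

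Third, intervals matter. The Discussion reasons from similar effect sizes between the new treatments and EMDR, so readers will want confidence intervals for the contrasts. Bonferroni supplies simultaneous ones directly and the closed test does not. This is a real but small cost.

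A reader might also draw stronger conclusions. One is that, because section 2.6 repeats no alpha, the comparisons may be run uncorrected, which would put familywise error at about 12% for one outcome at one occasion. The article does not support that: section 2.5 ties the three comparisons to the corrected level, nothing in section 2.6 contradicts it, and a condensed article may leave such detail to the full protocol or analysis plan. Another is that the remedy requires making CAPS-5 at T8 the only primary outcome. It does not. Section 2.4.1 names several primary instruments, and choosing among them is a separate design decision.

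**Conclusion.** The point holds as a modest efficiency gain. Bonferroni at 0.0167 is correct but more conservative than three arms require. For the three planned contrasts, Shaffer's procedure never rejects less and keeps familywise error at 5% or below. Power for a full-size pair rises by between 1 point (0.81 to 0.82, evenly spread arms) and 6 points (0.81 to 0.87, one arm different). In the latter pattern, power to find both true differences rises by 12 to 13 points (0.70 to 0.83).

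These figures rest on the plan's own assumptions: 39 evaluable per arm, d = 0.65, a quarter of the variance explained by baseline, and normal errors with equal variance. The dominance over Bonferroni rests on none of them, because it follows from the rule itself. The error guarantee applies to three contrasts on one outcome at one occasion. Neither this procedure nor 0.05/3 addresses multiplicity across several primary measures or across T8 and T12.

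**What to change.** In section 2.6.1.1, or in the analysis plan, state for the three pairwise post-treatment contrasts of section 2.5: if the smallest of the three two-sided p-values is at or below 0.0167, that pair is declared different and the other two are each tested at 0.05 two-sided; if it is above 0.0167, no difference is declared. Keep the sample size and describe it as conservative for this procedure. If the F-gated version is preferred for its slightly higher power, say so in advance and accept that it can occasionally miss a pair that Bonferroni would have found.

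The cost is a sentence or two of wording. Recruitment has begun and treatment allocation is open, so the change should be dated and recorded before any between-arm results are seen. If Bonferroni-adjusted intervals are shown alongside, add a note that they can include zero for a contrast declared significant. For example, a second pair with p = 0.03 would be declared different after the gate opens, while its 98.33% interval would still cover zero.

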### 2.6. Data analyses

The statistical analyses will be performed on an intention-to-treat basis. Pre-treatment group differences are assessed using one-way ANOVAs for continuous data and χ2 tests for categorical data. A multilevel model will be performed with Treatment Condition (EMDR therapy vs. EMDR 2.0 vs. Flash technique) and Time (weekly assessments during the treatment and bi-weekly assessments during the follow-up phase) as predictors in the model. Measurements are nested within participants. Multilevel models are preferred over a repeated-measures ANOVA as participants with missing data can be included. In Level 1 of the model, the outcome measures vary within participants over time. In Level 2 of the model, the intercepts and slopes of the growth trajectories vary between participants. All analyses will be performed using the statistical programs R (Version 4.2.2) and IBM SPSS (Version 28).

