### 2.3. Procedure

#### 2.3.1. Recruitment and screening

The study will be conducted at the Altrecht Academic Anxiety Center. Individuals with PTSD symptoms will be approached by their therapists to participate in the current study. If written consent has been given, the research assistant may contact individuals directly as well. Those who are interested in participating will be invited for an appointment with one of the research assistants. During this appointment, the study will be explained and patients who wish to participate are asked to sign an informed consent-form. After consent, the Life Events Checklist for the DSM-5 (LEC-5) will be administered, along with a screening questionnaire assessing age, completed education, previously followed trauma-focused treatment, medication use, alcohol- and drug use, and suicidality. If patients report suicidal thoughts, suicidality risk will be assessed using the suicidality module of the MINI. If patients report a high risk of suicidality on the MINI., a senior therapist trained in the assessment of suicidality will make a final decision about the participation. By administering the Clinician-Administered PTSD Scale for DSM-5 (CAPS-5) and the screening questionnaire containing questions about the in- and exclusion criteria, it will be determined whether patients meet the criteria for participation.

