#### 2.3.2. Randomization and allocation

After inclusion and the baseline assessment, participants will be randomly assigned to one of the three treatment conditions: EMDR therapy, EMDR 2.0, or the Flash technique, by means of permuted block randomization with block sizes of 3, 6 and 9 to be sure that group sizes are equal across conditions. Randomization will be performed by an independent researcher using an online tool. Stratified randomization will be performed with complex PTSD as stratification factor to ensure that patients with complex PTSD are equally distributed across conditions. There will be no blinding as participants and therapists will be able to tell which treatment arm they are allocated to. The CAPS-5 assessments, however, are conducted by assessors who are blind to the allocated treatment conditions.

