#### 2.3.3. Assessments

At baseline assessment (T0), the CAPS-5 will be administered by a trained therapist, along with the Life Events Checklist for DSM-5 (LEC-5). The International Trauma Questionnaire (ITQ), PTSD Checklist for DSM-5 (PCL-5), Dissociative Experiences Scale (DES), Beck Depression Inventory-II (BDI-II), Brief Symptom Inventory (BSI), and the Acceptance and Action Questionnaire-II (AAQ-II) will be administered digitally. The baseline assessment takes approximately 90 min. After the baseline assessment and the session where the treatment plan is drawn up, a 6-week treatment phase commences during which participants fill out questionnaires weekly prior to the treatment sessions (T1-6). Questionnaires include the PCL-5, BDI-II, BSI, and AAQ-II and take approximately 30 min in total to complete. After the first treatment session (T2), a questionnaire about treatment acceptability is administered. After the treatment phase, a 12-week phase commences where no actual treatment is delivered, but participants fill out the PCL-5, BDI-II, BSI, and AAQ-II bi-weekly (T7-12). The treatment acceptability questionnaire is administered again at T7. The CAPS-5, ITQ, and DES are administered 4 weeks after treatment is completed (T8), and 12 weeks after termination of treatment (T12). To minimize missing data, reminders will be sent out to the participants to fill out the questionnaires. For a complete overview of the timing of the interventions and assessments, see Figure 1.

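### Baseline differences between randomised arms are to be significance-tested: any significant result is a chance finding, and observed imbalances up to about 0.45 SD would go unflagged

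*Protocol article*

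**What the plan says.** Section 2.6 opens its analysis plan with a test of comparability: "Pre-treatment group differences are assessed using one-way ANOVAs for continuous data", and "χ2 tests for categorical data". It does not list the variables, give an alpha for these tests, or say what follows from a significant or a non-significant result.

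Section 2.3.2 says that patients are assigned after the baseline assessment, "by means of permuted block randomization with block sizes of 3, 6 and 9", and adds: "Stratified randomization will be performed with complex PTSD as stratification factor".

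Two places show which variables could be tested. Section 2.3.3 has the CAPS-5 and six questionnaires at baseline: the ITQ, the PCL-5 and four others ("Dissociative Experiences Scale (DES), Beck Depression Inventory-II (BDI-II), Brief Symptom Inventory (BSI), and the Acceptance and Action Questionnaire-II (AAQ-II) will be administered digitally"). Section 2.3.1 describes "a screening questionnaire assessing age, completed education, previously followed trauma-focused treatment, medication use, alcohol- and drug use, and suicidality".

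On adjustment, 2.6.1.1 (CAPS-5, ITQ, DES) and 2.6.1.2 (PCL-5, BDI-II, BSI, AAQ-II) enter the baseline value as a covariate, without conditions. Section 2.6.2 (a log-rank test on the number of sessions to reliable change and to a PCL-5 cut-off of 33) and 2.6.3 (a one-way ANOVA of acceptability items) name no covariate. None of the four sections names the complex PTSD stratum as an adjustment term.

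**The concern.** A significance test asks whether chance can explain a difference. When the groups were made by randomisation, chance is known to be the explanation, so the test has no useful answer to give. A significant result reports a difference between arms that reflects nothing but the draw, and it may lead readers to doubt valid contrasts. For complex PTSD the test is redundant as well, since stratified blocks keep the arms close to equal on it.

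A non-significant result is no better guide. The p-value depends on the size of the imbalance and on the number of patients, not on how strongly the variable predicts outcome. A moderate imbalance in a strong predictor can pass without comment.

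This matters most where no baseline covariate is planned. In 2.6.2 the event is reaching a fixed PCL-5 score, so a patient who starts closer to 33 has less distance to cover. A chance imbalance in baseline PCL-5 therefore bears on the efficiency comparison, for which section 1.4 states a directional expectation in favour of EMDR 2.0 over standard EMDR.

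**Working it through.** **Inputs from the article.** 130 patients are recruited in three equal arms, so 130/3 is about 43 per arm (2.5, 1.5). There are seven baseline scale scores (2.3.3) and about six screening items (2.3.1).

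**Inputs assumed.** Each baseline test is made at 0.05, there are 7 to 14 tests, and the seven scales correlate equally at 0 to 0.7. The article gives none of these. The only alpha it states belongs to the sample size: "Bonferroni-corrected alpha for the three pairwise comparisons = 0.0167 (0.05/3), power = 0.80 and Allocation ratio = 1".

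**The plan's own figure.** The sample size reproduces. Removing a quarter of the variance gives a standardised effect of 0.65/√0.75 = 0.751. A two-sided t-test at 0.05/3 then has power 0.792 with 38 per arm and 0.804 with 39. So n = 39, 3 × 39 = 117, and 117/0.90 = 130.

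**Chance of at least one significant baseline test.** For k independent tests this is 1 − 0.95^k. For correlated scales it comes from 20,000 simulated three-arm trials with 43 per arm, with the further items independent and treated as continuous.

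| Tests | Independent | Scales correlated 0.3 | 0.5 | 0.7 |
|---|---|---|---|---|
| 7 (scales only) | 30% | 27% | 24% | 19% |
| 12 (scales + 5 items) | 46% | 44% | 41% | 37% |
| 13 (scales + 6 items) | 49% | 47% | 44% | 40% |
| 14 (scales + 7 items) | 51% | 50% | 47% | 44% |

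The range is 19% to 51%. It depends on the number of tests, their alpha and their correlation. It does not depend on the number of patients.

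**What the tests fail to flag.** Here the number of patients does matter. With three arms of 43, the ANOVA has 2 and 126 degrees of freedom and a critical F of about 3.07. The smallest observed difference that reaches it, in SD units, is:
- one arm apart from two equal arms: √(2 × 3.07 / (43 × 2/3)) = 0.46;
- arms evenly spread, lowest to highest: √(2 × 3.07 / (43 × 1/2)) = 0.53.

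As an example, take arm means of −0.2, 0 and +0.2 SD, a gap of 0.40 SD between the outer arms. Then F = 43 × (0.04 + 0.04)/2 = 1.72 and p = 0.18, so it is not flagged. The standard error of a difference between two arms is √(2/43) = 0.216 SD, so 0.40 SD is 1.85 standard errors. For one variable and one given pair of arms, chance alone produces a gap at least that large about 6% of the time.

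**Where an unflagged imbalance would carry through.**

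| Analysis | Baseline value of the outcome as covariate? |
|---|---|
| 2.6.1.1 CAPS-5, ITQ, DES | Yes, unconditionally |
| 2.6.1.2 PCL-5, BDI-II, BSI, AAQ-II | Yes, unconditionally |
| 2.6.2 Sessions to PCL-5 of 33 or reliable change | No; log-rank test |
| 2.6.3 Acceptability items | No; no baseline value exists, as the first rating follows the first session (2.3.3) |

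The article gives no figure from which the effect of a baseline PCL-5 imbalance on the log-rank comparison could be computed, so that effect is not quantified here.

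**The case against.** The strongest reply is that the tests do nothing. No covariate, model or decision depends on them, and the models for the main outcomes adjust for baseline whatever they show. That stands, and it limits the point to reporting and to the comparisons without a covariate.

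Several stronger readings are tempting, and the article does not support them.

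- A reader might infer that close to half of such trials would report a false difference. That needs about 12 or 13 independent tests at 0.05. The article gives no list and no alpha, and it describes the screening questionnaire as serving the eligibility criteria; nothing says that all its items will be compared between arms.
- A reader might tie that rate to the size of this trial. Trial size governs only which imbalances are missed.
- A reader might carry a 0.40 SD imbalance into the main result. With a correlation of √0.25 = 0.5 it would move an unadjusted mean contrast by 0.40 × 0.5 = 0.20 SD, or 0.20/0.65 = 31% of the target effect. No planned contrast of symptom-scale means between arms is unadjusted, and the quarter of variance in 2.5 refers to the CAPS-5, so this describes no planned analysis.
- A reader might infer that covariates will be chosen after the tests, or that non-significant imbalances will be declared absent. The article says neither.

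The redundant test for complex PTSD is harmless, because stratification makes a significant result unlikely.

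**Conclusion.** The point holds as a minor flaw. The planned tests cannot inform about arms formed by randomisation. Under the stated assumptions, at least one chance finding is expected in roughly 19% to 51% of trials. With about 43 per arm, observed imbalances up to about 0.45 SD are not flagged, whatever their importance for outcome.

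The primary and secondary symptom models are not at risk from this, since their baseline adjustment is fixed in advance. What is exposed is the baseline report, which may present chance as a difference, and the efficiency comparison in 2.6.2, where baseline PCL-5 affects time to the cut-off, no adjustment is planned, and a non-significant baseline test would be no reassurance.

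**What to change.** In 2.6, replace the sentence on pre-treatment differences with a statement that baseline characteristics are presented by arm as means (SD) or counts, without significance tests, and that covariates are fixed in advance whatever imbalance is seen. Then name them:

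- **2.6.1.1 and 2.6.1.2:** the baseline value of the outcome, as already planned, plus the complex PTSD stratum used in the randomisation.
- **2.6.3:** the complex PTSD stratum only, because acceptability has no baseline value.
- **2.6.2:** either a log-rank test stratified by complex PTSD, or a Cox or discrete-time model with baseline PCL-5 and the stratum. Only the model deals with baseline PCL-5, and a discrete-time version suits time counted as one to six sessions.

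The cost is one replaced sentence, short additions to the later sections, and slightly more analysis work in 2.6.2 and 2.6.3. No useful information is lost by dropping the tests.

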##### 2.6.1.2. Outcome measures PCL-5, BDI-II, BSI, and AAQ-II

For the outcome measures administered (bi)-weekly, a multilevel model will be performed. The baseline values will be included as covariate in the model. It will be investigated if the treatment conditions are effective in reducing self-reported PTSD symptoms (PCL-5), comorbid symptoms (BDI-II and BSI) and experiential avoidance (AAQ-II) over time. To investigate the differential effectiveness of the treatments, a Time × Condition interaction will be tested with the outcome measures as dependent variables. To investigate the effectiveness of the treatments, the effect of time will be tested with the outcome measures as dependent variables.

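### For the PCL-5 and the other (bi)weekly outcomes, a Time × Condition test on one growth slope across treatment and follow-up does not measure the post-treatment difference, and can miss or reverse it when arms differ in speed

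*Protocol article*

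**What the plan says.** Section 2.6 (Data analyses) of the protocol article names a multilevel model with Treatment Condition and Time as predictors. Time covers both the weekly assessments in treatment and the two-weekly ones afterwards. The random part is described thus: "In Level 2 of the model, the intercepts and slopes of the growth trajectories vary between participants".

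Section 2.6.1.2 applies this to the PCL-5, BDI-II, BSI and AAQ-II, with baseline as covariate. The deciding test is: "To investigate the differential effectiveness of the treatments, a Time × Condition interaction will be tested with the outcome measures as dependent variables". For effectiveness as such: "To investigate the effectiveness of the treatments, the effect of time will be tested with the outcome measures as dependent variables".

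Section 2.3.3 gives the schedule. T1–T6 are weekly, each before a session. Then: "After the treatment phase, a 12-week phase commences where no actual treatment is delivered", with T7–T12 every two weeks. T8 is 4 weeks and T12 is 12 weeks after treatment.

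Section 2.4.1 lists the PCL-5 among the primary measures. Section 2.6.1.1 handles CAPS-5, ITQ and DES differently: condition means are estimated and compared at T8 and T12.

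**The concern.** Symptom scores that fall during treatment and then hold do not follow one straight line over 18 weeks. If one line is fitted to such a course, its slope depends on when the fall happens as well as on its size. The sooner an arm reaches its plateau, the more of its visits lie on the flat part and the flatter its slope. A difference in slopes is then not a difference in benefit.

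Section 2.5 powers the trial on something else, a difference in means at the post-treatment occasion. The slope test may therefore have far less power than the planned 80% for the PCL-5, or in some courses reach significance for the slower arm.

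A smaller point concerns the effect of time. In a model that also holds Time × Condition, this single term describes either an average over arms or the reference arm, depending on the coding. Section 1.4 expects every intervention to be effective, which needs one statement per arm.

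**Working it through.** **1. The plan's own figure.** Section 2.5 gives "Bonferroni-corrected alpha for the three pairwise comparisons = 0.0167 (0.05/3), power = 0.80 and Allocation ratio = 1", a "medium to large effect size *d* = 0.65", a two-sided test, and a baseline covariate from which "we expect to explain approximately a quarter of the variance at the post-treatment measurement". The adjusted effect is 0.65/√(1 − 0.25) = 0.751. With the noncentral t distribution, power is 0.792 at n = 38 and 0.804 at n = 39 per arm. So n = 39, N = 117, and 117/0.90 = 130. The sample size reproduces. It rests on a post-treatment mean difference, not on a slope.

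**2. Assumptions for the slope (not in the protocol).** T1–T6 at weeks 0–5; T7–T12 at weeks 8, 10, 12, 14, 16, 18. Mean scores fall linearly and then stay level. The slower arm falls 1.5 SD by week 6.

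**3. Fitted slope.** Slope = Σ(w − w̄)y / Σ(w − w̄)². Here w̄ = 93/12 = 7.75 and Σ(w − w̄)² = 1139 − 12 × 7.75² = 418.25. Measuring y from the plateau leaves only the early visits in the numerator.
- Plateau at week 3: −(7.75 × 1.5 + 6.75 × 1.0 + 5.75 × 0.5) = −21.25. Slope −0.0508 SD/week; × 18 = −0.91 SD.
- Plateau at week 6: −(7.75 × 1.5 + 6.75 × 1.25 + 5.75 × 1.0 + 4.75 × 0.75 + 3.75 × 0.5 + 2.75 × 0.25) = −31.94. Slope −0.0764 SD/week; × 18 = −1.37 SD.

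Both arms end at the same level and the faster one is never behind, yet its slope is flatter. To match the slower arm's slope, the week-3 arm would need a fall of 1.5 × 31.94/21.25 = 2.25 SD. That is 0.75 SD better at the end, more than the design effect of 0.65. For plateaus at weeks 4 and 5 the break-even falls are 1.89 and 1.66 SD.

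The order for week 3 against week 6 is the same if time is coded by occasion number (−1.35 against −1.88 points per occasion for a 20-point fall).

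**4. Consequence for the test.** Simulation: 4,000 trials per cell, 39 per arm, alpha 0.05/3. Patient intercept SD was 0.7, response SD 0.5 and residual SD 0.5, which gives √(0.49 + 0.25 + 0.25) ≈ 1 SD in total at follow-up. Per-patient slopes were compared with adjustment for T0. Each pair of results is without and with an extra random slope of SD 0.05 SD/week.

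| Faster arm's plateau (slower: week 6) | Equal final benefit: significant for the slower arm | Faster arm 0.65 SD better: significant for the faster arm |
|---|---|---|
| Week 3 | about 85% / 28% | about 0% / 0% |
| Week 4 | about 35% / 11% | about 15% / 5% |
| Week 5 | about 7% / 3% | about 68% / 21% |
| Week 6 (same speed) | nominal level | about 95% / 46% |

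For the same 0.65 SD advantage, the baseline-adjusted contrast at T8 is significant in about 85% of trials without the extra random slope and about 70% with it, whatever the plateau time.

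**5. Check in PCL-5 points with a mixed model.** Assumed: a 20-point fall in both arms, plateau at week 3 against week 6, random-slope SD 0.5 points/week, residual SD 6. The mean interaction was +0.33 points/week, and 75% of 20 runs were significant at 0.05 for the slower arm. With slope SD 0.3–1.0 and residual SD 6–10, the calculated chance at 0.0167 runs from 15% to 88%.

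**6. A single knot does not repair it.** With a knot at week 6 and equal 1.5 SD falls, the fitted treatment-phase slopes are −0.245 (faster) and −0.250 SD/week (slower). The faster arm still does not look faster. Means by occasion show it ahead during treatment and level afterwards.

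**The case against.** The word linear is nowhere in section 2.6, and the quoted sentence describes what varies between participants. Time might be coded by occasion or by phase in an analysis plan that is not shown, and with categorical time the problem disappears. This stands as a limit on certainty. But the article itself names the Time predictor, the slopes and the deciding test, and for CAPS-5, ITQ and DES it sets out comparisons by occasion. One slope is therefore the plain reading for the other measures.

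A reader might infer that the protocol predicts the reversal, because section 1.4 expects EMDR 2.0 to be more efficient than EMDR. The documents do not support that. Efficiency is a separate aim with its own survival analysis (section 2.6.2), section 1.4 states no prior expectation on differential effectiveness, and nothing foresees a plateau halfway through treatment. Section 2.2.1, where memories are treated one after another over six sessions, fits continued improvement equally well.

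A reader might also take the 85% as the size of the problem. It belongs to the most extreme case shown. With a later plateau or more variable slopes the risk of a wrong direction is small, and loss of power becomes the main effect.

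Lastly, arm-specific time effects can be drawn from a model with an interaction, and section 2.6.1.2 does ask whether the conditions are effective. That the planned test pools the arms is an inference from its wording, so this part is secondary.

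**Conclusion.** The concern holds in conditional form. On its plain reading, the test for the PCL-5, BDI-II, BSI and AAQ-II targets a slope over two unlike phases and not the post-treatment difference behind the sample size. When one arm levels off earlier at a similar or modestly better level, the test loses power or can favour the slower arm. Under the assumed curves, significance in the wrong direction ranges from about 3% to 85% with equal final benefit. With a true 0.65 SD advantage for the faster arm, power ranges from about 0% to 68%. There is little loss only when both arms have the same speed and slopes vary little.

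The percentages rest on assumed curves and variances. The order of the fitted slopes depends on the curves alone.

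It would go too far to say that the primary analysis as a whole fails. The CAPS-5, ITQ and DES comparisons at T8 and T12, the sample size and the survival analysis are not touched.

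**What to change.** In sections 2.6 and 2.6.1.2:
- Treat time as categorical (measurement occasions) for the PCL-5, BDI-II, BSI and AAQ-II, and keep the baseline covariate.
- Make the between-arm contrast at T8 the test of differential effectiveness, with T12 secondary. This matches section 2.6.1.1.
- Report change from T0 for each arm by model contrasts, in place of one overall effect of time.
- Do not rely on a single knot at the end of treatment, since it does not recover a difference in speed.

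The cost is a change of wording and a few more estimated parameters; no new data are needed. If time was always meant to be categorical, one sentence saying so, together with the named T8 contrast, settles the point.
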